### Objectives and outcomes

#### Primary objectives

To determine the incidence of reversible left ventricular systolic dysfunction (as a proxy for Takotsubo stunning) in patients hospitalised for AECOPD at Sahlgrenska University Hospital (Gothenburg, Sweden).To investigate in-hospital clinical manifestations of AHF (defined as Killip class >1, table 1) in patients with signs of Takotsubo stunning versus those without, among patients hospitalised for AECOPD at Sahlgrenska University Hospital.

**Table 1 T1:** Killip classification of acute left-sided heart failure, based on clinical signs supported by chest imaging

Killip class I	No clinical/radiological signs of heart failure.
Killip class II	Clinical and radiological signs of heart failure but not pulmonary oedema (distinct bilateral rales or crackles over lungs suggesting interstitial fluid supported by interstitial fluid on chest X-ray*).
Killip class III	Clinical picture of frank pulmonary oedema supported by radiological* signs.
Killip class IV	Cardiogenic shock or hypotension (measured as systolic blood pressure lower than 90 mm Hg) and evidence of peripheral vasoconstriction (oliguria, cyanosis or sweating).

* Pulmonary ultrasound may be used to confirm Killip class.

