#### ECG and chest X-ray

Examinations with ECG and chest X-ray are performed in hospital the same day/days as echocardiography. These procedures are performed in accordance with clinical routine.

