### Collection of data

After IC, data as declared below are collected (also summarised in table 2, schedule of events). If investigations have been performed after contact with healthcare but before IC (ie, after arrival of ambulance/arrival to emergency department/hospital ward but before IC), these data may be included as study data provided that the IC is signed, to avoid unnecessary repeats of investigations/procedures.

**Table 2 T2:** Schedule of events

Schedule of events	Admission	Inclusion (day 0) (within 72 hours of admission)	Day 1 24±6 hours*	Day 2 48±12 hours*	Day 3 72±12 hours*	In hospital (including date)	Postdischarge within 6 months
Eligibility criteria and informed consent		X					
Time from admission to inclusion		X					
GOLD grade (1–4) and group (A, B, E)		X					X
Severity of COPD exacerbation (mild, moderate, severe)^18^		X					
Baseline characteristics including baseline medication	X	X					
Blood pressure and heart rate	X	X	X	X	X		X
Pulse oximetry and respiratory rate	X	X	X	X	X		X
Body temperature	X	X	X	X	X		
Blood work-up (clinical routine)	X†	X†					X
Symptom questionnaire		X					
Echocardiography (standard clinical protocol)		X	(X)‡				(X)‡ day 30 (±48 hours)
NT-proBNP	X†	X	(X)‡				
Biobank (if separate consent)		X					
12-lead ECG	X†	X	(X)‡				
Chest X-ray	X†	X	(X)‡				
Exacerbation-specific treatment	X	X	X	X	X		
Complications and outcome	X	X	X	X	X	X	X
Spirometry, diffusion capacity, body plethysmography							X
6-minute walk test. COPD assessment test, mMRC							X

* After inclusion.

† When available.

‡ Only if positive in screening.

COPD, chronic obstructive pulmonary disease; GOLD, Global Initiative for Obstructive Lung Disease; mMRC, modified Medical Research Council Dyspnea Scale; NT-proBNP, N-terminal pro-B-type natriuretic peptide.

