### Outcomes

#### Primary outcomes

Cumulative incidence of reversible RWMA or reversible left ventricular systolic dysfunction (as proxy for Takotsubo stunning) according to screening and follow-up echocardiography.Clinical signs of AHF during hospitalisation (defined as Killip class >1, table 1, components of classification documented in hospital medical chart).

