### Patient and public involvement

This study originates from the person-centred care context at Sahlgrenska University Hospital, where patient perspectives are a central part of everyday clinical work, in accordance with the hospital’s core value explicitly phrased in the hospital policy: ‘For the patient, with the patient’. Through ongoing dialogue with patients, previously unrecognised clinical needs and gaps in existing knowledge were identified, which influenced the study objectives. This is particularly relevant since the majority of investigators and collaborators in this study are also treating physicians for the included patients. Patients and the public were not otherwise involved in the study design or conduct.

Results of the study will be disseminated through scientific publications and presentations. In addition, findings will be communicated in formats accessible to patients and the public, including plain language summaries and dissemination through relevant clinical settings where patients receive care.

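### The primary acute heart failure outcome is not ascertained equally: only screening-positive patients get a scheduled day-1 chest X-ray, and Killip II and III need radiological support

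*Protocol article*

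**What the plan says.** **Outcome.** The Primary outcomes section of the protocol article defines the second primary outcome as "Clinical signs of AHF during hospitalisation (defined as Killip class >1, table 1, components of classification documented in hospital medical chart". The window is the whole hospital stay.

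**Killip classes (Table 1).** Class II is "Clinical and radiological signs of heart failure but not pulmonary oedema", spelled out as "distinct bilateral rales or crackles over lungs suggesting interstitial fluid supported by interstitial fluid on chest X-ray". Class III is "Clinical picture of frank pulmonary oedema supported by radiological" signs. Class IV is "Cardiogenic shock or hypotension (measured as systolic blood pressure lower than 90 mm Hg) and evidence of peripheral vasoconstriction", and no imaging is named. The Killip classification section says that class combines clinical findings with chest imaging, and that lung ultrasound is used in a subset where the class is uncertain.

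**Schedule (Table 2).** Chest X-ray is marked for all patients at day 0, and at admission when available. The day-1 film carries the footnote "Only if positive in screening". The ECG and chest X-ray section agrees: "Examinations with ECG and chest X-ray are performed in hospital the same day/days as echocardiography". Under Cardiac screening, only screening-positive patients have repeat echocardiography.

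**Analysis.** The Statistical plan and sample size section takes a positive screening result as the exposure and Killip-defined acute heart failure (AHF) as the outcome, in a logistic model adjusted for baseline confounders.

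**Contrast within the plan.** The Secondary outcomes section limits ECG and NT-proBNP to admission and inclusion, time points that both groups share. The primary Killip outcome has no such limit.

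**The concern.** The exposure itself triggers an additional measurement that feeds the outcome. Take two patients with the same crackles and a clear day-0 film. If one is screening-positive, a second film is scheduled about 24 hours later, and interstitial fluid on it completes class II. The screening-negative patient is imaged again only if someone orders a film in routine care. The same true course can therefore be Killip II in one group and Killip I in the other.

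The error runs in the direction of the study hypothesis. It arises after exposure and because of it, so age, sex and other baseline covariates do not address it. The second primary objective compares patients with and without Takotsubo stunning. That comparison inherits the problem, because every stunning case is drawn from the screening-positive group.

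**Working it through.** **1. The plan's own figure.** Inputs from the Statistical plan section: N = 150, ratio 1:10, 30% versus 5%, α = 0.05 (taken as two-sided) and 80% power.
- Groups: 150/11 = 13.64 positives and 136.36 negatives.
- Pooled proportion: (0.30 + 10 × 0.05)/11 = 0.0727.
- Standard error under no difference: √[0.0727 × 0.9273 × (1/13.64 + 1/136.36)] = 0.0738.
- Standard error under the alternative: √[0.30 × 0.70/13.64 + 0.05 × 0.95/136.36] = 0.1255.
- Power: Φ[(0.25 − 1.96 × 0.0738)/0.1255] = Φ(0.84) = 0.80.

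The stated design reproduces. The planned contrast rests on about 14 × 0.30 = 4.2 AHF events in positives and 136 × 0.05 = 6.8 in negatives.

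**2. Scheduled chances to meet the imaging component of class II or III**

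| | Screening-positive | Screening-negative |
|---|---|---|
| Admission film | when available | when available |
| Day-0 film | yes | yes |
| Day-1 film | yes | no |
| Later film in routine care | possible | possible |

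The only scheduled difference is the day-1 film.

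**3. Size under an assumed range.** The documents do not say how often the day-1 film would complete a Killip II or III. Assume true AHF incidence is 5% in both groups and that the extra film adds d percentage points of detected Killip >1 in positives only. The odds ratio is [(0.05 + d)/(0.95 − d)] / (0.05/0.95), and the expected extra events are 14 × d. The last two columns give the chance of a significant result at two-sided 0.05 with no true difference, by exact enumeration of 14 versus 136 patients. These two tests stand in for the planned logistic model.

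| d | Detected in positives | Spurious OR | Extra events | Chi-square | Fisher |
|---|---|---|---|---|---|
| 0 | 5% | 1.00 | 0 | 4.9% | 2.0% |
| 2.5 points | 7.5% | 1.54 | 0.35 | 10.7% | 5.4% |
| 5 points | 10% | 2.11 | 0.70 | 18.1% | 10.6% |

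**4. Where the range comes from.** If the day-1 film were a second, independent 5% chance, detection would be 1 − 0.95² = 9.75%, which is 4.75 extra points (OR 2.05) and 14 × 0.0475 = 0.67 extra events. If half of that is lost to dependence between looks, detection is 0.05 + 0.5 × 0.0475 = 7.4%, with OR 1.51 and about 0.33 extra events. Both are illustrations. The protocol's 5% is a whole-stay incidence in negatives, not a probability per look.

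**The case against.** The best counter-argument is that a film alone cannot create an event, because classes II and III also need clinical signs. Shared surveillance is also substantial. All patients have a day-0 film and vital signs to day 3, and AHF is collected as a dated complication in everyone. A control with new signs can still be imaged. A film 24 hours after another is far from an independent look. All of this stands and argues for a modest bias. It does not remove the scheduled difference.

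A reader might also infer more than the documents support:
- **That the day-1 ECG and NT-proBNP inflate the outcome too.** Neither is a Killip component. They could act only by prompting closer examination.
- **That every Killip >1 depends on imaging.** Class IV names none.
- **That Killip class is assigned by someone who knows the echo result.** The Patient and public involvement section says that "the majority of investigators and collaborators in this study are also treating physicians for the included patients", and echo views are saved in the chart, so this is possible. The article does not say who assigns the class or what they have seen. It is inference, and such arrangements are commonly left to the full protocol.
- **That patients with only crackles or only X-ray change are classed at will.** Class II requires both, so under Table 1 they are not Killip >1. The wording gap lies in class I and does not affect the dichotomy analysed.
- **That one or two extra events should be expected.** The assumed range gives fewer than one.

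Finally, discarding the day-1 film outright could create the opposite bias. If a positive patient develops signs on day 1, the protocol film may replace one that would have been ordered anyway, while a control's routine film for the same signs would count. That objection is sound, and the fix allows for it.

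**Conclusion.** The asymmetry is in the text and affects a primary outcome. Screening-positive patients have one more scheduled opportunity than screening-negative patients to meet the imaging component of Killip II or III, and nothing in the article confines the outcome to examinations that both groups receive. The expected direction is upward, and baseline adjustment cannot correct it.

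The size cannot be derived from the documents. On an assumed 2.5 to 5 extra points against a true 5% in both groups, the spurious odds ratio is about 1.5 to 2.1. That is well short of the planned contrast, whose odds ratio is (0.30/0.70)/(0.05/0.95) = 8.1, but enough to raise the chi-square false-positive rate from about 5% to between 11% and 18%. The point rests on the day-1 chest X-ray alone.

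**What to change.** Reword the primary Killip >1 outcome before analysis:
- **Primary:** use examinations scheduled for both groups (admission data, day-0 examination and day-0 film), plus later imaging in either group where new clinical signs were recorded in the chart. A day-1 protocol film counts only when such signs are documented. Class IV, which names no imaging, is scored alike in both groups.
- **Sensitivity, prespecified:** Killip >1 from admission and day-0 data only.
- **Secondary:** Killip >1 including all day-1 protocol films.
- **Where feasible, for patients still to be enrolled:** record the day-0 Killip class before the study echo result is opened. This cannot be applied to the 56 patients already included.

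**Cost.** No extra tests or visits, and N = 150 is unchanged. The work is a change to a primary outcome definition during enrolment, which should be documented as such, and scoring from dated chart entries. Slightly fewer AHF events will be counted in positives, some possibly genuine. Imaging ordered because a positive echo raised suspicion remains in the whole-stay version, which is why the day-0 sensitivity analysis is needed beside it.

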#### Secondary outcomes

In-hospital 3-point major adverse cardiac events (MACE): non-fatal myocardial infarction, non-fatal stroke or cardiovascular death (according to hospital medical chart).Admission to intensive care unit (according to hospital medical chart).In-hospital all-cause death (according to hospital medical chart).Respiratory failure, acute or acute on chronic (hypercapnia with acidosis, PaCO_2_ >6.0 and pH <7.35, according to lab values in hospital medical chart).ST elevation, ST depression, QT prolongation, T-wave inversion on ECG (ECG at admission and inclusion).Level of NT-proBNP (obtained at admission and inclusion).One-year all-cause and cardiovascular death (Swedish Cause of Death Register, National Board of Health and Welfare).

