#### Secondary objectives

The secondary objectives include comparisons between patients with AECOPD with and without evidence of Takotsubo stunning. These analyses will be conducted in a hypothesis-generating framework to present new possible mechanistic pathways and clinical associations, focusing on the following variables:

In-hospital and 1-year all-cause mortality, in-hospital complications (acute myocardial infarction, stroke, pulmonary embolism (PE), respiratory failure, clinical deterioration leading to intensive care unit admission) and length of hospital stay.ECG (ST elevation, ST depression, QT prolongation, T-wave inversion).N-terminal pro-B-type natriuretic peptide (NT-proBNP) in plasma.Presenting symptoms (prevalence of chest pain, severity of dyspnoea).Echocardiographic signs of right ventricular strain.

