### Statistical plan and sample size

Inclusion is planned over approximately 3 years to estimate the cumulative incidence of Takotsubo stunning in patients hospitalised for AECOPD. The primary analysis will assess the association between a positive screening result and clinical manifestations of AHF using multivariable logistic regression. The model will adjust for relevant baseline confounders, with a significance threshold of α=0.05.

For the primary analysis, the required sample size is estimated at 150 patients, assuming a 1:10 ratio of positive to negative screening results. In previous research randomly investigating the correlation between clinical and echocardiographic signs of heart failure, clinical heart failure was present in approximately 50% of patients with echocardiographic left ventricular systolic dysfunction (LVEF <40%).^23^ Given the higher cut-off for systolic dysfunction in CATCH (LVEF <50%) and inclusion of newly detected RWMA as positive screening (ie, also in absence of reduced LVEF), together with the exclusion of patients with prior type 1 myocardial infarction or known persistent systolic dysfunction, we conservatively estimate the proportion of clinical heart failure in the positive screening group to approximately 30%. Accordingly, our sample provides 80% power to detect a difference in the incidence of clinical signs of AHF between the groups, assuming 30% in the positive screening group and 5% in the negative screening group with α=0.05.

Secondary and tertiary outcomes will be analysed using linear regression for continuous outcomes and logistic regression for dichotomous outcomes, in both unadjusted and adjusted models. A Cox proportional hazards model adjusted for baseline confounders will be applied to analyse 1-year mortality. These analyses are considered explanatory or hypothesis generating. Results will be reported as effect estimates with 95% CIs and unadjusted p values, with false discovery rate correction applied to account for multiple comparisons.^24^

Unadjusted and adjusted analyses (including covariates age and sex) will be presented as separate models. A sample size of 150 patients, with an assumed 1:10 ratio of positive to negative screening results, translates to a total number of 15 events. Given the relatively low number of expected events, all further adjustment will include only clinically meaningful covariates and will be presented as separate models.

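### The QT outcome is named as a yes/no finding, which discards information when the case group is very small; the corrected QT interval could be analysed with the linear model already planned (low priority)

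*Protocol article*

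**What the plan says.** The Secondary objectives of the protocol article list "ECG (ST elevation, ST depression, QT prolongation, T-wave inversion" as one item of the comparison between patients with and without evidence of Takotsubo stunning. The Secondary outcomes repeat the four signs and add the time points: "ST elevation, ST depression, QT prolongation, T-wave inversion on ECG (ECG at admission and inclusion". The next item there is worded as a quantity: "Level of NT-proBNP (obtained at admission and inclusion".

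The section Statistical plan and sample size assigns the model by type of outcome: "linear regression for continuous outcomes and logistic regression for dichotomous outcomes, in both unadjusted and adjusted models". It also sets the status of these analyses ("These analyses are considered explanatory or hypothesis generating") and the handling of multiplicity ("with false discovery rate correction applied to account for multiple comparisons").

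On availability, the section ECG and chest X-ray says: "Examinations with ECG and chest X-ray are performed in hospital the same day/days as echocardiography". Table 2 accordingly schedules a 12-lead ECG at inclusion for every patient, and marks the admission ECG as taken when available.

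**The concern.** ST elevation, ST depression and T-wave inversion are naturally recorded as present or absent. Prolongation of QT is a cut placed on a measured interval. Listing it with the other three makes it a dichotomous outcome by its wording, and the model rule then points to logistic regression. The contrast with NT-proBNP, which is named as a level, supports that reading.

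Cutting a continuous measure discards information, and here the comparison has little to spare. The smaller group is limited to the few screening-positive patients, and the Cardiac screening section narrows it further to those with reversible dysfunction and no alternative cause. A yes/no QT result would rest on a handful of prolonged cases and give an imprecise odds ratio, above all after adjustment for age and sex. A difference in repolarisation is one of the signals the secondary objectives look for, and it would be harder to see.

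**Working it through.** **1. Size of the groups.** The plan states that "the required sample size is estimated at 150 patients, assuming a 1:10 ratio of positive to negative screening results". One part in eleven gives 150 / 11 = 13.6, about 14 positive against 136 negative. The plan's own count of 15 is 150 / 10. Both count screening-positives, so they are upper limits for stunning cases.

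**2. The plan's own figure.** Inputs are 30% v 5%, ratio r = 10, 80% power and alpha 0.05 (taken as two-sided). The pooled proportion is (0.30 + 10 × 0.05) / 11 = 0.0727.

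n₁ = [1.96 √(0.0727 × 0.9273 × 1.1) + 0.8416 √(0.30 × 0.70 + 0.05 × 0.95 / 10)]² / 0.25² = (0.534 + 0.390)² / 0.0625 ≈ 13.7

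This rounds up to 14 positives and 154 patients in all. With 14 v 136 the power is 80.5%. The stated 150 patients and 80% are therefore reproduced to within rounding, and 14 v 136 is a fair basis for the QT comparison.

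**3. Assumptions for QT.** The documents state no effect, SD, prevalence or power for QT. Assumed here: a normal corrected QT interval with equal SD, a uniform shift of d SD in cases, a share p₀ of controls above the cut, and two-sided 0.05 without false discovery rate correction.

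**4. Continuous analysis, 14 v 136.** Power ≈ Φ(d / √(1/14 + 1/136) − 1.96), where the root is 0.2807.
- d = 0.5: Φ(1.781 − 1.96) = 43%
- d = 0.8: Φ(2.850 − 1.96) = 81%
- d = 1.0: Φ(3.563 − 1.96) = 95% (94% by the t distribution)

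**5. Yes/no analysis.** The share of cases above the cut is p₁ = 1 − Φ(Φ⁻¹(1 − p₀) − d). For example, p₀ = 10% and d = 0.5 give p₁ = 21.7%, or 14 × 0.217 ≈ 3 prolonged cases; p₀ = 30% and d = 1.0 give 68.3%, or about 10.

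Simulated power (20,000 runs), t-test against the likelihood-ratio test of the dichotomy:

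| Shift | Continuous | Yes/no, p₀ = 10% | Yes/no, p₀ = 20% | Yes/no, p₀ = 30% |
|---|---|---|---|---|
| 0.5 SD | 42–43% | 24% | 28% | 30% |
| 0.7 SD | 69–70% | 43% | 49% | 52% |
| 0.8 SD | 81% | 54% | 61% | 63% |
| 1.0 SD | 94% | 74% | 80% | 82% |

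The loss is about 12 to 27 points.

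**6. Sensitivity.**
- Fewer cases: with 7 cases v 136 on the same grid, the loss is about 5 to 22 points. The continuous analysis itself has only 25% power at 0.5 SD.
- Another test: the pooled normal approximation for two proportions gives 10 to 26 points for d = 0.5 to 0.8 and p₀ = 5 to 30%. At d = 0.4 and p₀ = 20% it gives 6.5.
- Another shape of effect: suppose only 30% of 14 cases prolong, by 2 SD. Power is then 52–53% continuous, against 51% yes/no with a cut at the control upper 5% and 49% at the upper 10%, a loss of 1 to 4 points. With a 20% cut the loss is about 14. If those 30% shift by 3 SD and the cut is at 5%, the yes/no test is marginally ahead (76% v 75%).

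**The case against.** The strongest reply is that the article never says how QT will be coded. A reader might infer that QT is to be analysed only as yes/no, and that the interval is already recorded in ms for every patient. Neither is stated: the plan assigns models by outcome type without classifying QT, and the ECG section describes examinations under clinical routine. An analysis plan that is not shown could add the interval. This stands, and the point is limited to what the published wording naturally implies. For the same reason the absence of a cut-off for prolongation is no fault of the article.

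A reader might also take 14 as the number of stunning cases, or the power loss as a property of this study. The first is wrong, because 14 counts screening-positives before reversibility and alternative causes are considered. The second is unsupported, because the range depends on an assumed uniform shift, which favours the continuous test; the subset scenario shows that the loss can vanish.

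Finally, the outcome is exploratory, and power is poor under either form if the effect is modest. With 14 cases and 0.5 SD, the continuous analysis has 43% power at 0.05 and about 21% at an illustrative 0.01; with 7 cases it has 25% and 10%. That stands too, and limits the priority. It does not justify discarding information: an analysis reported as estimates with confidence intervals gains from the more precise measure.

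**Conclusion.** The point holds in a limited form. As worded, the QT outcome is naturally a yes/no variable for logistic regression, although the interval behind it can be read from an ECG scheduled for all patients and a linear model for continuous outcomes is already in the plan. Under a uniform shift of 0.5 to 1.0 SD with 10 to 30% of controls above the cut, the cost is about 12 to 27 points of power with 14 cases and about 5 to 22 with 7. It may be close to nil if only a subset of cases prolongs and the cut is strict. None of these inputs comes from the documents. The point concerns one item of a hypothesis-generating secondary outcome and touches neither the primary analysis nor the sample size, so the priority is low.

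**What to change.** In the Secondary objectives and Secondary outcomes, add the heart-rate-corrected QT interval (ms) as the main QT outcome. Analyse it on the inclusion ECG by the linear regression already planned, unadjusted and adjusted for age and sex. Use the admission ECG in a supplementary analysis where it is available, since the outcome list includes that time point. Keep QT prolongation (yes/no) as a supporting outcome. The rate-correction formula and the cut for prolongation should be fixed before analysis, and the analysis plan is the right place for them.

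The change needs no extra patients, visits or examinations; the interval has to be read from ECGs that are already scheduled. The main QT result becomes a mean difference in ms instead of an odds ratio, and one exploratory secondary outcome of a registered study is restated during recruitment. According to Study status, 56 of 150 patients were enrolled and analysis follows the end of inclusion, so the change can still be made and documented beforehand.
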